## Aims of the project

To determine the sustained impact of HHE and annual GP training, alone and in combination, at 7 years, including 5 years of post intervention follow-up on:

a) Primary

i) BP levels of all participants.

ii) Cardiovascular morbid events and all cause mortality in the high risk cohort.

b) Secondary

i) Behavioural risk factors including diet, physical activity, weight and tobacco use in all trial participants

ii) Clinical risk factors for CVD including plasma glucose and lipids, and albuminuria in the high risk cohort.

iii) Left ventricular (LV) mass index and diastolic dysfunction in the high risk cohort.

## Hypotheses:

We hypothesize that at 6 years of follow-up:

- Children and young adults randomized to HHE versus no HHE will continue to have lesser rise in BP.
- Hypertensive adults randomized to HHE plus trained GP intervention will continue to have greater decline in BP than single or no intervention. They will also have experience greater decline in plasma glucose, serum cholesterol and urine albumin excretions levels, and have lower left ventricular mass index and less diastolic dysfunction.

## Ancillary Studies:

- a) To determine the influence of BP and antihypertensive therapy on quality of life in the high risk cohort
- b) To evaluate the use of practice guidelines for management of hypertension among practitioners in the randomized communities.
- c) To examine the relationship between BP variability during 2 years of intervention with LV mass index and cardiovascular morbidity and mortality at 7years.

# METHODS

All participants in the trial (originally aged 5 and now 13 years or over) will be visited by trained field staff masked to randomization status. However, the individuals (children or individuals aged 15 – 39 years) not enrolled in the main study, pregnant women, bed ridden and/or mentally retarded study subjects unable to consent will be excluded. Eligibile subjects will be offered informed consent. The date and time for interview will be set at individual’s convenience after obtaining informed consent. Information on socioeconomic status assessed via household possessions and income, occupation and literacy status, diet, physical activity (modified IPAQ), and tobacco use would be collected and weight, height, waist and hip circumference would be measured. In addition, questionnaires on health related quality of life (SF-36 and EQ-5D) will be administered to all subjects aged 40 and over with hypertension after translation in Urdu and pre-testing. As collected during baseline, the names and doses of current anti-hypertensive medications will be recorded.

As during the COBRA trial, BP will be measured with a calibrated automated device, Omron HEM-737TM Intellisense BP Monitor, in the sitting position after 5 minutes of rest using an appropriate sized paediatric or adult cuff, as applicable.[51](#_ENREF_51) BP measurements will be repeated after two weeks. Three consecutive readings will be taken at each visit, and the mean of the final two used in the analysis. The visits will be balanced across the four randomised groups and planned during the first half of the day to minimise seasonal and diurnal variation in measurements, respectively. Maximum three visits will be paid for those not present at a scheduled date and thereafter, they will be labelled as lost to follow-up.

Since one of the main aims the post-trial follow-up is to track the cohort for morbidity and mortality, a special field team will be dedicated to tracking those who were lost to follow-up during the initial 2 years or have relocated within the city of Karachi. We expect to recapture about 15% of those lost to follow-up with the assistance of neighbours, family members and community leaders residing in the study clusters. As Karachi is considered the business and economic hub of Pakistan with an annual population growth rate of 5%, the rate of out-migration is expected to be very low.[52](#_ENREF_52),[53](#_ENREF_53) Details of current residential address will be recorded for the possibility of shifting into another randomised cluster, although the chances are minimal as they represent 12 out of 5000 (0.24%) geographical communities in Karachi.

In all subjects in the high risk cohort (aged 40 years and above with hypertension), fasting blood sample will be collected for plasma glucose (Synchron Cx-7/Delta, Beckman, US) and lipid profile (Hitachi-912, Roche Japan). A fresh morning urine sample will also be collected for albumin (measured using nephelometry by the Array Systems method on a Beckman Coulter) and urine creatinine (Synchron Cx-7/Delta, Beckman, US). For external quality control on albumin measurements, AKUH laboratory routinely sends samples to Bio-Rad Laboratories Inc, Irvine, CA. Sera and urine samples will be stored at -70 freezer for possible future analysis.

A trained sonographer (gender-specific as culturally appropriate) will perform 2-D echocardiogram with a portable device for measurement of left ventricular mass and function (see 3.1.1). All assessments will be performed to a standard protocol that conforms to international standards for definitions and measurements.

## Assessment of left ventricular mass and diastolic dysfunction:

This will be done at the field site using the portable Philips CX50 imaging system by a sonographer with recommended level of training for performing echocardiograms. One sonographer routinely performing echocardiograms will undergo standardized training including didactic presentations and hands-on supervised studies.[54](#_ENREF_54) The exam will be performed with the subjects in semi-recumbent in the left lateral position. Left ventricular measurements will be performedusing M-mode from the parasternal long axis according to the American Society of Echocardiography guidelines.[54](#_ENREF_54) Left ventricular internal dimension and wall thicknesses will be measured at end-diastole and end-systole by American Society of Echocardiography recommendations using a computerized review station, and then reviewed by a cardiologist certified by the U.S. National Board of Echocardiography.[54](#_ENREF_54) As in the LIFE Study, end-diastolic left ventricular septal and posterior wall thicknesses and internal dimensions will be used to calculate left ventricular mass by the formula: left ventricular mass = 1.04 x 0.8 [(left ventricular wall thicknesses + internal dimension) – (internaldimension)] + 0.6 g. left ventricular mass index (LVMI),calculated as left ventricular mass in grams divided by body surface area in square meters.[39](#_ENREF_39)

Doppler imaging: Transmitral Doppler inflow signals will be acquired and peak early diastolic velocity (E), peak late diastolic velocity (A), the E/A ratio, pulmonary vein, mitral valve deceleration time (DT), isovolumic relaxation time (IVRT) will be measured. In addition, Tissue Doppler imaging (TDI) of mitral valve annulus in the 4 chamber view at the septal and lateral walls will be performed as per guidelines of the American Society of Echocardiography, from which peak early (E’ or Ea) and peak late (A’ or Aa) diastolic mitral annular velocities will be measured.[55](#_ENREF_55) The E/E’ ratio, will be computed as a reflection of left atrial pressure as a measure of left ventricular diastolic function.[56](#_ENREF_56) In addition, patients will be categorized into grades of left ventricular diastolic dysfunction (none, grades I, II and III) based on established criteria.[56](#_ENREF_56) A subset of 100 subjects, stratified by sex, will be invited for a repeat measurement within one month to assess reproducibility (limits of agreement/coefficient of variation for test-re-test repeatability of LVMI and tissue Doppler parameters. Intra-observer variation in archived measurements from the same day will also be reported).[57](#_ENREF_57)

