### Rationale for sub-clinical CVD outcome – LV mass and diastolic dysfunction

Increased left ventricular mass is established sequelae of uncontrolled hypertension, and a modifiable predictor cardiovascular morbidity and mortality. Hypertension also leads to heart failure by causing functional abnormality in relaxation of the myocardium, manifested as diastolic dysfunction. This can be present with or without concomitant increase in left ventricular mass. Studies on asymptomatic hypertensive subjects have demonstrated significant increase diastolic dysfunction assessed via measures of decreased left ventricular relaxation, increased stiffness and filling pressures.[41](#_ENREF_41),[42](#_ENREF_42)

Our previous pilot experience on echocardiographic evidence of left ventricular mass in 320 randomly selected community based subjects revealed higher LVMI in women compared to men: the mean (SD) was 75.7 (25.9) [median 72.9] g/m(2) in women and 72.0 (19.2) [median 71.1] g/m(2) in men.[43](#_ENREF_43) This is not entirely surprising as women in Pakistan have a greater burden of cardiovascular risk factors associated with left ventricular mass including obesity, hypertension (and less likely to be screened for it), and metabolic syndrome than men.[6](#_ENREF_6) However, we also observed that the increased risk in women could not be entirely explained by conventional cardiovascular risk factors. Studies on LVMI using echocardiography in Indo-Asian population are scarce. Further, we did not assess diastolic dysfunction. Thus, the proposed study provides a unique opportunity for rigorous assessment of left ventricular mass and diastolic dysfunction according to intervention status and BP lowering in women and men recruited to COBRA. The demonstration of benefit particularly in women, will underscore the importance of targeting this vulnerable segment of the population in hypertension screening and CVD prevention programmes.

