## Outcome Measures

*Primary:*

In all subjects:

- Change in systolic BP from baseline to mean of two post trial follow-up visits.
- Composite of CVD morbid events and all-cause mortality.

*Secondary:*

In all subjects:

- Change from baseline to post trial follow-up in the following: body mass index (BMI), waist hip ratio, current tobacco use, total physical activity, and dietary intake of fruit and vegetables.

In the high risk cohort

- Percent change in plasma glucose (and incident pre-diabetes or diabetes defined as (fasting plasma glucose 100 mg/dl (5.5mmol/L) or more or initiation of hypoglycaemic agent)[58](#_ENREF_58), total and LDL cholesterol (and incident hyperlipidemia defined as total serum cholesterol >=200 mg/dl (5.18 mmol/L); LDL cholesterol >=130 mg/dl (3.37mmol/L))[59](#_ENREF_59), albumin excretion rate (and incident albuminuria defined as spot urine albumin to creatinine ratio of 30mg/g or greater)[60](#_ENREF_60) , and estimated glomerular filtration rate from baseline to post trial follow-up;
- Left ventricular mass index and E/A’ ratio at post trial follow-up.[39](#_ENREF_39),[61](#_ENREF_61)

Ancillary:

In the high risk cohort

- Overall mean score on Patient Health Related Quality of Life (HRQOL) based on 36-Item Short-Form Survey.

Data Collection and Management

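### As shown, the left ventricular mass formula carries no exponents, so the internal dimension cancels and the line cannot give the protocol's own pilot LVMI values

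*Protocol*

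**What the plan says.** Section 2.1 (Assessment of left ventricular mass and diastolic dysfunction) introduces the calculation with "As in the LIFE Study, end-diastolic left ventricular septal and posterior wall thicknesses and internal dimensions will be used to calculate left ventricular mass" and then prints the formula: "left ventricular mass = 1.04 x 0.8 [(left ventricular wall thicknesses + internal dimension) – (internaldimension)] + 0.6 g". The index is "calculated as left ventricular mass in grams divided by body surface area in square meters". No unit is given for the wall thicknesses or the internal dimension, and no other section gives a formula for mass.

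Section 1.3.4 reports a pilot in 320 randomly selected community subjects, in whom "the mean (SD) was 75.7 (25.9) [median 72.9] g/m(2) in women and 72.0 (19.2) [median 71.1] g/m(2) in men".

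Section 2.4 (Outcome Measures) lists as a secondary outcome in the high risk cohort "Left ventricular mass index and E/A’ ratio at post trial follow-up". LVMI also appears in the secondary aims (1.4), the hypotheses (1.5), the outcome models (3.1) and the ancillary analysis of blood pressure variability (1.6 and 3.2).

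**The concern.** The bracket in the formula adds the internal dimension to the wall thicknesses and then takes the same internal dimension away. Without exponents nothing of chamber size is left. The result is a multiple of a length plus a constant, yet the protocol treats it as grams.

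The line is the only stated definition of a secondary outcome. If a programmer followed it literally, two hearts with equal walls but very different chambers would receive the same mass. The randomised comparison labelled LVMI would then compare wall thickness divided by body surface area.

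**Working it through.** **Inputs from the protocol.** The formula and the LVMI definition (2.1); the pilot means of 75.7 and 72.0 g/m2 (1.3.4).

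**Inputs assumed.** The protocol gives no wall thickness, internal dimension, body surface area (BSA) or unit. WT denotes septal plus posterior wall thickness, and ID the internal dimension. The ranges used are WT 1.4-2.6 cm, ID 3.5-5.5 cm and BSA 1.5-1.9 m2.

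**1. The formula as shown**

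- Mass = 1.04 x 0.8 x [(WT + ID) - ID] + 0.6 = 0.832 x WT + 0.6.
- With WT 1.7 cm, mass is 0.832 x 1.7 + 0.6 = 2.01 g for ID 3.5, 4.5 and 5.5 cm alike.

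**2. Can it reproduce the pilot means?**

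- In cm, lowest: (0.832 x 1.4 + 0.6)/1.9 = 0.93 g/m2. Highest: (0.832 x 2.6 + 0.6)/1.5 = 1.84 g/m2.
- In mm, lowest: (0.832 x 14 + 0.6)/1.9 = 6.45 g/m2. Highest: (0.832 x 26 + 0.6)/1.5 = 14.82 g/m2.
- Working backwards, 72.0 g/m2 at BSA 1.5 needs WT = (72.0 x 1.5 - 0.6)/0.832 = 129.1, and 75.7 g/m2 at BSA 1.9 needs (75.7 x 1.9 - 0.6)/0.832 = 172.2. A wall-thickness sum of 129-172 is impossible in cm and implausible in mm.

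The pilot figures are therefore not reproduced in either unit.

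**3. Which exponent fits?** Take one assumed heart: walls 0.9 + 0.9 cm, ID 4.5 cm, BSA 1.7 m2, so WT + ID = 6.3 cm.

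| Exponent on both terms | Mass (g) | LVMI (g/m2) |
| --- | --- | --- |
| none (as shown) | 0.832 x 1.8 + 0.6 = 2.1 | 1.2 |
| 2 | 0.832 x (39.69 - 20.25) + 0.6 = 16.8 | 9.9 |
| 3 | 0.832 x (250.05 - 91.13) + 0.6 = 132.8 | 78.1 |
| 4 | 0.832 x (1575.3 - 410.1) + 0.6 = 970 | 571 |

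Of these, only the cube is of the pilot's size, and only the cube turns the bracket into a volume. Over WT 1.5-2.0 cm, ID 4.2-4.6 cm and BSA 1.6-1.7 m2, the cubed form gives about 55-99 g/m2, which covers both pilot means. So the correction follows from the protocol's own figures and does not depend on looking up the cited study.

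**4. What would be lost if the line were followed.** Walls 1.0 + 1.0 cm, BSA 1.7 m2:

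- ID 4.0 cm: as shown (0.832 x 2.0 + 0.6)/1.7 = 1.33; cubed (0.832 x (216 - 64) + 0.6)/1.7 = 74.7 g/m2.
- ID 6.0 cm: as shown 1.33; cubed (0.832 x (512 - 216) + 0.6)/1.7 = 145.2 g/m2.

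The cubed index nearly doubles between these two hearts; the line as shown cannot tell them apart.

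**The case against.** The strongest reply is that this may not be an error in the plan at all. The text was read from PDF by a program, and characters are visibly missing elsewhere: the comparison sign before the age limit in the high-risk approach (1.2.2), and the unit after the freezer temperature (Methods). The sentences around the formula contain run-together words, and a raised digit after a closing bracket is easily lost. Some characters that were probably raised do survive as plain text, such as the trademark letters on the blood pressure monitor and the power in the variability metric (3.2). These are letters, however, and may have been typed flat, so they do not settle the matter. This objection stands: loss in extraction is neither shown nor excluded.

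The second reply concerns the consequence. A reader might infer that the trial's LVMI will in fact be a rescaled wall thickness of about 1 g/m2. The protocol does not support that. It ties the calculation to an earlier study and the measurements to echocardiography guidelines, has a certified cardiologist review them, and reports plausible pilot LVMI values. Literal coding is unlikely, and values near 1 g/m2 would probably be noticed. The figure also presumes centimetres and typical dimensions, none of which the protocol states.

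A third reply is that the unit of the dimensions could be left to an analysis plan or echocardiography manual. That is fair as a complaint on its own. It is worth adding only because the line may need correcting anyway and the result depends on the unit.

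What the replies do not remove is that the protocol commits to calculating mass by a specific formula, and that formula, as shown, conflicts with the protocol's own pilot values.

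**Conclusion.** The point holds as a low-severity correction, conditional on the source file. It is certain from the algebra that the line as shown drops the internal dimension and is linear in wall thickness. Coded as shown, it would give LVMI of about 1-2 g/m2 in cm or about 6-15 g/m2 in mm, under the assumed WT of 1.4-2.6 cm and BSA of 1.5-1.9 m2. Neither range comes near the pilot means of 72.0 and 75.7 g/m2, and no plausible choice of dimensions closes the gap.

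It is not established that the exponents are missing from the sponsor's file, or that anyone has coded or will code the line literally. No sample size, power figure or reported result in the protocol depends on it. The affected quantities are one secondary outcome and one of the outcomes in the blood pressure variability analysis.

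**What to change.** 1. Check the formula in the source file. If both bracketed terms carry the exponent 3 there, nothing in its algebra needs correcting.
2. If they do not, replace the line in section 2.1 with: LV mass (g) = 0.8 x 1.04 x [(septal + posterior wall thickness + internal dimension)^3 - (internal dimension)^3] + 0.6, with all dimensions taken at end-diastole and in cm.
3. Before analysis, run the programmed formula and compare its output with the pilot values in section 1.3.4. Use these as a check of scale, not as a target, because the pilot was a community sample and the outcome is measured in adults with hypertension.

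The cost is one line in the protocol, a check of the analysis program and no new data.

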## Assessment of morbid and mortal events:

As during the main trial, all subjects aged 40 years and above in the cohort will be tracked for assessment of morbid CVD events requiring hospitalizations or death during the entire 6 years of follow-up. Since data from the initial 2 years were collected at 6 monthly intervals, relevant information during the last 4 years will be extracted from district-level official mortality registers in each cluster to track mortality. A standardized questionnaire on mortality or hospital admission during the last four years will be administered in a culturally sensitive fashion. In cases of death, the cause of death reported by the nearest family member will be recorded, and the WHO verbal autopsy questionnaire will be administered. Complete death records will be extracted, where available. However, some degree of uncertainty is expected with ascertainment of cause of death is expected in capturing mortality data on verbal autopsy from beyond the last one year. All those who report admission to hospital for a cardiovascular event, or a stroke like event will be subsequently evaluated by a study cardiologist or neurologist to confirm the diagnosis per recommendations of the American Heart Association and the European Society of Cardiology.[21](#_ENREF_21) On ethical grounds, all these patients will also be given advice regarding treatment for any complications, and prevention of future events.

## Ancillary Study- Survey of General Practitioners:

The data collectors masked to randomization status will approach all GPs practicing in the 12 randomized clusters to administer a standardized questionnaire. It will contain questions on six basic themes: a) type of practice: average number of patients seen, b) information about the GP: gender, years into practice, c) detection of high BP: whether BP is measured on all or all new patients, how many readings and when, criteria for diagnosing high BP, and whether these criteria differ for the elderly as opposed to young adults, d) evaluation of patients with high BP: whether laboratory investigations for coexisting conditions (diabetes, hyperlipidemia, kidney failure) are obtained on hypertensive patients, e) management of hypertension: patient education regarding deleterious effects of hypertension, advice on non-pharmacological measures to control hypertension, the level of BP that is targeted during treatment, and choice of antihypertensive medications, and f) types of antihypertensives used (generic or branded), g) whether antihypertensives are discontinued once BP is controlled.

## Outcome Measures

*Primary:*

In all subjects:

- Change in systolic BP from baseline to mean of two post trial follow-up visits.
- Composite of CVD morbid events and all-cause mortality.

*Secondary:*

In all subjects:

- Change from baseline to post trial follow-up in the following: body mass index (BMI), waist hip ratio, current tobacco use, total physical activity, and dietary intake of fruit and vegetables.

In the high risk cohort

- Percent change in plasma glucose (and incident pre-diabetes or diabetes defined as (fasting plasma glucose 100 mg/dl (5.5mmol/L) or more or initiation of hypoglycaemic agent)[58](#_ENREF_58), total and LDL cholesterol (and incident hyperlipidemia defined as total serum cholesterol >=200 mg/dl (5.18 mmol/L); LDL cholesterol >=130 mg/dl (3.37mmol/L))[59](#_ENREF_59), albumin excretion rate (and incident albuminuria defined as spot urine albumin to creatinine ratio of 30mg/g or greater)[60](#_ENREF_60) , and estimated glomerular filtration rate from baseline to post trial follow-up;
- Left ventricular mass index and E/A’ ratio at post trial follow-up.[39](#_ENREF_39),[61](#_ENREF_61)

Ancillary:

In the high risk cohort

- Overall mean score on Patient Health Related Quality of Life (HRQOL) based on 36-Item Short-Form Survey.

Data Collection and Management

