In children and young adults, the age related rise in systolic BP was significantly attenuated in those randomized to HHE versus no HHE.[2](#_ENREF_2) In those at high risk (40+ with hypertension), we observed that the combined strategies (HHE plus trained GP) had the most marked beneficial impact on BP.[3](#_ENREF_3) However, the trial was of short duration and it is not known whether the benefit of interventions on BP observed at 2 years would be sustained in the medium term in the post-trial period. We now wish to conduct 4 year post trial follow-up of all the COBRA trial participants, with intensive efforts to contact all those lost to follow-up, to determine the sustained impact of our interventions on a) BP levels and cardiovascular morbidity and mortality; b) behavioural risk factors (tobacco use, diet, weight, physical activity); and clinical risk factors (plasma glucose, lipids and albuminuria) for CVD; and sub-clinical cardiovascular outcomes (left ventricular mass and diastolic dysfunction) in the trial participants. We will also assess adherence to hypertension treatment guidelines by the practitioners, and influence of BP and antihypertensive therapy on quality of life of these subjects. In addition, the relationship of repeated BP measurements over time with clinical and sub-clinical cardiovascular outcomes will be examined.

Thus, the post trial follow-up of COBRA participants will provide valuable insights on the presence of sustained benefit of interventions after their discontinuation. This information is key for up-scaling a national programme modelled on similar interventions for Pakistan, which has been proposed to the Federal Ministry of Health, and is potentially scalable in neighbouring countries. The study would also be novel in advancing the knowledge on the relationship of BP with robust clinical and sub-clinical cardiovascular outcomes in Indo-Asians.

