## Rationale

### Rationale for following up BP and CVD morbidity and mortality:

The main trial was designed to assess the impact of family based HHE delivered every three months to the households in the randomized clusters. We found that this strategy was beneficial at the end of 2 years in lowering BP. However, we could not draw conclusions on the post trial effect of our intervention, whether they are lost or sustained at the same or an augmented level. Long term follow-up of trial participants after discontinuation of intervention in other studies have yielded conflicting results. For example, in the United Kingdom Prospective Diabetes Study (UKPDS) the benefit of tight control of BP on mortality was lost at 10 years.[22](#_ENREF_22) There are concerns that life style modifications may be difficult to sustain in the absence of continuous re-enforcement. Even in dietary interventions with overall success from nutrition counselling, subjects tend to regain weight after an initial decline.[23](#_ENREF_23) However, the characteristics of developing country populations can be substantially different in terms of level of education (50% literate in Pakistan) and diet (high salt consumption at 8 grams/day), than those in the industrialized world where most trials are conducted.[24](#_ENREF_24),[13](#_ENREF_13) The same applies to GPs in the communities, in whom serious deficiencies in knowledge and practices were identified.[15](#_ENREF_15) Thus, part of the success of our strategies could be due to the greater scope for improvement in knowledge and behaviour in the study population. Therefore, we expect most lifestyle changes to be retained and reflected in sustained benefit on BP. The post trial benefit of life style intervention on diabetes prevention in China supports our contention although admittedly impacts on a different outcome, hypertension, could differ.[25](#_ENREF_25) Although there is strong evidence to expect substantive benefit in CVD outcomes from reduction in BP[26](#_ENREF_26) considerable dissociation between the impact on BP and cardiovascular morbidity and mortality has been observed in some studies. For example, in the Antihypertensive and Lipid-Lowering to Prevent Heart Attack Trial (ALLHAT), a federally funded study, the combined CVD outcomes were disproportionately greater in doxazosin versus chlorthalidone arm (4-year rates, 25.45% versus 21.76%; Relative Risk ,1.25; 95% CI, 1.17-1.33; P<0.001) than expected from a 2 mmHg difference in systolic BP.[27](#_ENREF_27) More recently, the Avoiding Cardiovascular Events through Combination Therapy in Patients Living with Systolic Hypertension (ACCOMPLISH) trial was stopped prematurely at a median follow-up of 3 years when a significant difference was observed in CVD events: 9.6% in the benazepril–amlodipine group 11.8% in the benazepril-hydrochlorothiazidegroup; a relative risk reduction of 19.6% (p<0.001); despite no difference in BP between the two groups.[28](#_ENREF_28) At the same time, it is also important to note that mortality benefit in the Multiple Risk Factor Intervention Trial (MRFIT) was apparent only during post trial monitoring, despite significant reduction in BP during the 7 year in-trial phase.[29](#_ENREF_29) Thus, other pleotropic benefits of interventions in addition to BP reduction can contribute to some of that benefit. Finally, as mentioned above, successes or failures of the developed countries may not be exportable to developing ones, where significant differences exist in the population characteristics and healthcare systems.[30](#_ENREF_30) Therefore, post trial follow up of COBRA is needed to assess any benefit of our interventions after their discontinuation on sustained lowering of BP, and its translation into reduction in CVD morbidity and mortality in the Pakistani population. The extended follow-up of these outcomes will also enable the determination of the relationship between the duration of BP lowering on CVD outcomes. This information will be most valuable in up-scaling strategies for BP control and CVD prevention, and designing new interventions for further improvement in Pakistan, and neighbouring countries.

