## Primary & Secondary Outcomes:

For the main intention to treat analysis, the mean estimated value in each cluster for those with missing values at the final visit will be computed for all individuals with available measurements, and assigned to those with missing last follow-up measurements for individuals by cluster. This method of imputation of missing values has been shown to yield valid inferences and is recommended for large community intervention trials with small size clusters.[63](#_ENREF_63),[64](#_ENREF_64) The primary and secondary outcomes will be compared between randomised clusters using a nested mixed factorial design analysis of variance. Due to previously detected significant interaction between treatment assignments on BP in the high risk group, only four-way analysis will be performed in that group.[65](#_ENREF_65) A p value of <0.05 was considered to be statistically significant for the main effects. We will report the means and 95% confidence intervals for the treatment effects, adjusted for sex, age and baseline BP in the models. In addition, models will also be constructed after accounting for the baseline and post-trial measurement of fasting plasma glucose, and lipids (as indicated). In the model for CVD morbidity and mortality, albuminuria, LVMI, and E/E’ ratio we will also adjust for change in systolic BP from baseline to follow-up. The marginal adjusted probabilities will be used to calculate the risk ratios, and their 95% CI will be computed by the bootstrapping method.[66](#_ENREF_66)

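### The rationale asks whether the 2-year BP effect was lost, held or augmented, but the planned BP comparison can show only whether a between-group difference persists

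*Protocol*

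**What the plan says.** The question appears in three forms.

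- Section 1.3.1 (Rationale for following up BP) says the main trial left open, for the effect after the interventions ended, "whether they are lost or sustained at the same or an augmented level". The Background says "it is not known whether the benefit of interventions on BP observed at 2 years would be sustained in the medium term".
- Section 1.4 (Aims) is more general: "To determine the sustained impact of HHE and annual GP training, alone and in combination, at 7 years".
- Section 1.5 (Hypotheses) is narrower: "Children and young adults randomized to HHE versus no HHE will continue to have lesser rise in BP", and hypertensive adults given both interventions "will continue to have greater decline in BP than single or no intervention".

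The primary BP outcome in section 2.4 is "Change in systolic BP from baseline to mean of two post trial follow-up visits". Section 3.1 compares it between randomised groups by a nested mixed factorial analysis of variance, with treatment effects and 95% CIs "adjusted for sex, age and baseline BP in the models". In the high risk cohort the comparison is four-way.

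Follow-up BP from the 2-year trial has one planned use: the ancillary BP-variability analysis in section 3.2, which covers the high risk cohort. No analysis uses the 2-year BP of participants aged 5 to 39.

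**The concern.** *Lost*, *same level* and *augmented* each describe the post-trial effect relative to the effect at 2 years. An outcome measured from the pre-intervention baseline to the post-trial visits, tested against no difference, does not estimate that relation. It can show that some difference is present now. It cannot say whether that difference is as large as before, smaller or larger, and failing to show a difference is not evidence that the effect has gone.

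The Background presents the persistence of benefit as key to scaling up a national programme. A programme that keeps its full effect after it stops and one that keeps half of it could both yield a significant result. The 2-year BP that would help to tell them apart is already held for 78% of the high risk cohort and 72% of those aged 5 to 39 (section 1.2.3).

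**Working it through.** **Inputs.** Section 1.2.3 gives the 2-year SBP decline (95% CI) in the high risk cohort:

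- both interventions: 10.8 (8.9 to 12.8)
- HHE only: 5.6 (3.7 to 7.4)
- trained GP only: 5.6 (3.7 to 7.5)
- neither: 5.8 (3.9 to 7.7)

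Section 1.2.3 also gives an interaction p of 0.004. The significance level is 0.05 (section 3), taken as two-sided.

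**Check that the inputs are usable.** SE = CI width / 3.92, giving 0.995, 0.944, 0.969 and 0.969, with groups treated as independent. The interaction is 10.8 − 5.6 − 5.6 + 5.8 = 5.4. Its SE is √(0.995² + 0.944² + 0.969² + 0.969²) = 1.94, so z = 2.78 and p = 0.005. That is close to the stated 0.004 given rounding.

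**The 2-year effect, both versus neither.** 10.8 − 5.8 = 5.0. SE = √(0.995² + 0.969²) = 1.39, 95% CI 2.3 to 7.7.

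**What the planned test can tell apart.** The post-trial SE is not given. I assume 1.39, and 20% more (1.67) as a range. Power ≈ Φ(effect/SE − 1.96), plus a negligible opposite tail except at zero effect.

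| True post-trial effect (mm Hg) | Power, SE 1.39 | Power, SE 1.67 |
|---|---|---|
| 7.5 (augmented) | >99% | 99% |
| 5.0 (same) | 95% | 85% |
| 2.5 (halved) | 44% | 32% |
| 0 (lost) | 5% | 5% |

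Same and augmented both usually give significance. A halved effect falls either way. An observed difference of 2.5 with SE 1.39 has a 95% CI of 2.5 ± 2.7, or −0.2 to 5.2, which includes both zero and the full 2-year effect.

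**Participants aged 5 to 39.** The 2-year difference is 1.5 − 0.1 = 1.4 mm Hg, p = 0.02. The group CIs in that table imply an SE of about 0.29 and a p far below 0.02, so I take the SE from the p value: 1.4 / 2.33 = 0.60. If the post-trial SE is the same, a fully retained effect is significant with probability Φ(2.33 − 1.96) = 64%. It would be non-significant 36% of the time.

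**What a direct contrast would add.** For the post-trial minus 2-year effect, SE = √(S₂² + Sₚ² − 2ρS₂Sₚ), where S₂ and Sₚ are the SEs of the two estimates and ρ their correlation (unknown, taken as 0 to 0.7).

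- Sₚ = 1.39: SE 1.96 to 1.08. Power to detect halving (or growth to 7.5) is 25% to 64%, and complete loss 72% to above 99%.
- Sₚ = 1.67: SE 2.17 to 1.21. Power is 21% to 54%, and 63% to 98%.

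All of these use a normal reference. With 12 clusters in four cells, an analysis at cluster level has about 12 − 4 = 8 degrees of freedom and a critical value of 2.31 instead of 1.96, so real power would be lower.

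**The case against.** The three-way wording sits in a rationale and describes what the main trial could not conclude. The hypotheses ask whether groups continue to differ, and the same rationale section ends by asking for any benefit after the interventions stopped. The planned comparison answers that, keeps the randomised contrast, and reports effects with 95% CIs that can be read beside the 2-year results. **This stands.** A reader might infer that the study cannot answer its question at all; the aim and hypotheses do not support that.

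A reader might also infer that p<0.05 will be reported as sustained and p>0.05 as lost. The protocol states no such rule.

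A group-by-time model may be in an analysis plan not shown here, and the team fitted a time-by-treatment term to the in-trial data (section 1.3.5). So the missing model is not in itself an error. What remains is that this document poses a relative question and fixes an outcome and main analysis for a narrower one.

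The extra contrast is also weak. Basing the verdict on its p value, with no margin, would let a non-significant change pass as sustained, which is the same mistake in another place. **This stands** and shapes the fix.

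Reading the two sets of results side by side is possible but informal. It ignores the within-person correlation, and the participants actually observed differ through deaths, new losses and the expected recapture of about 15% of those lost (section 2). In the high risk cohort the 2-year result rests on a single final-visit reading and the new one averages two visits. That affects precision; it does not by itself bias the difference between groups, and the added model would not remove it.

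**Conclusion.** The point holds as a mismatch between the relative question in section 1.3.1 and the outcome and analysis in sections 2.4 and 3.1. It is not a fault in the primary outcome, and no stated figure is wrong. As fixed, the analysis can show that a difference persists. It cannot distinguish a same, reduced or augmented effect, and it cannot establish loss from a non-significant result.

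For both interventions versus neither, the planned test would be significant in about 95% of studies with the effect intact, above 99% with it augmented to 7.5 mm Hg, and 44% with it halved. These figures assume a post-trial SE equal to the 2-year SE, independent groups and a normal reference. This is a worthwhile, inexpensive improvement rather than an essential correction.

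**What to change.** Keep the primary outcome and its comparison. In section 3.1, add a pre-specified secondary repeated-measures analysis:

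- Outcomes: SBP at 2 years and at post-trial follow-up, adjusted for baseline SBP, age and sex, with randomised group, time and group × time.
- Clustering: account for the randomised clusters, with degrees of freedom suited to 12 clusters.
- Populations: fit it separately for ages 5 to 39 (HHE versus no HHE) and the high risk cohort (four groups), and state who enters each model.
- Report: the group difference at each time, and the change between the two with its 95% CI.
- Interpretation: read that interval as an estimate. A non-significant change is not to be called sustained, nor a non-significant post-trial difference lost.
- Limits to state: the imprecision (about 25% to 64% power to detect halving, under the assumptions above), and the single 2-year reading against the mean of two visits in the high risk cohort.

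The alternative is to narrow section 1.3.1 to whether a between-group difference persists.

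The cost is one further model on 2-year data already held and post-trial data already planned, or one edited sentence. No extra visits or participants are needed.
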